### Participant Timeline

All participants will undergo in-person assessments over the course of 3 visits conducted at 6-month intervals. During the first visit, the participants will be screened and randomly assigned to 1 of 2 groups: OTC HAs and traditional HAs. Each HA will be fitted according to the guidelines described in the “Interventions” section before conducting the main tests. Subsequently, the participants will undergo main tests and be instructed to use the HA for at least 6 hours daily throughout the intervention period. After 6 months, the participants will return to the clinic for assessments using the same tests from the first visit as an intermediate evaluation. During the final visit (after 6 months), the participants will undergo the same evaluations as during the second visit and return the HAs. If participants experience any discomfort or issues with HA usage during the study period, they will be encouraged to visit the clinic at any time for adjustments (Table 1).

**Table 1 table1:** Timeline for this study.

Outcomes					Screening and baseline			After 6 months			After 1 year			
**Study consent**					✓			—^a^			—			

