### Assignment to Intervention Groups

After inclusion, the patients will be randomly assigned to 1 of 2 intervention groups: OTC HAs or traditional HAs. Randomization will be performed electronically using R software (R Core Team) with block randomization and an equal allocation ratio of 1:1. The block sizes will be 2 and 4. The researchers will remain blinded to the randomization sequence. However, due to the nature of the intervention, it is not possible to blind the participants and care providers to their assigned group.

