### Outcome Measurements

The participants will be screened using otoscopy, tympanometry, PTA, and WRS at the first visit (baseline). The participants who pass the screening tests will undergo main tests, including functional gain, REM, speech audiometry, and questionnaires at every visit.

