#### Main Tests

##### Functional gain

Functional gain will be measured by comparing the hearing thresholds at predetermined frequencies before and after wearing the HAs in a double-walled soundproof booth. The functional gain is theoretically equivalent to the real-ear insertion gain measured through REM. By comparing the functional gain at each frequency with the fitting formula for HA, we can determine the appropriateness of the HA fitting.

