##### Questionnaires

The Korean version of the Abbreviated Profile of Hearing Aid Benefit (K-APHAB) consists of a total of 24 items divided into 4 subscales of ease of communication, reverberation, background noise, and aversiveness to measure HL in everyday situations. For each item, a 7-point Likert scale is used (always=1 [99%]; never=7 [1%]). The benefit of the HA will be calculated as unaided scores minus aided scores [15]. The Korean version of the international outcome inventory for hearing aids (K-IOI-HA) is composed of 7 questions designed to subjectively evaluate the performance of HAs solely based on daily use, benefit, residual activity, satisfaction, residual participation restrictions, impact on others, and quality of life. Each item is rated on a 5-point scale, with higher scores indicating greater benefit. The total score ranges from 0 to 35 points [16].

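### The stated visit 1 order puts the unaided reference tests after randomisation and fitting, so participants give those reference values knowing their allocation

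*Protocol article*

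**What the plan says.** The Participant Timeline section sets the order of the first visit in three sentences. First, "During the first visit, the participants will be screened and randomly assigned to 1 of 2 groups". Next, "Each HA will be fitted according to the guidelines described in the “Interventions” section before conducting the main tests". Last, "Subsequently, the participants will undergo main tests and be instructed to use the HA for at least 6 hours daily". The Outcome Measurements section defines that last block: participants who pass screening "will undergo main tests, including functional gain, REM, speech audiometry, and questionnaires at every visit".

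Several of these tests have an unaided half. Functional gain is obtained by "comparing the hearing thresholds at predetermined frequencies before and after wearing the HAs in a double-walled soundproof booth". The Speech Audiometry section compares both the word score in quiet and the K-HINT threshold with and without the aids. For K-APHAB, the Questionnaires section says: "The benefit of the HA will be calculated as unaided scores minus aided scores".

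On blinding, the Assignment to Intervention Groups section says that "it is not possible to blind the participants and care providers to their assigned group". It adds that researchers are blinded to the randomisation sequence. It does not say whether the people who run the tests know the allocation.

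Table 1 has a single column for screening and baseline. It gives one row per main test, with no separation of unaided and aided parts.

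**The concern.** A benefit score is a difference between an unaided and an aided value. In an open-label trial the unaided value can be protected from knowledge of the allocation simply by taking it before randomisation. The stated order gives up that protection. By the time the unaided parts are run, the participant knows the arm and has either self-fitted a device or had one fitted by an audiologist. Behavioural thresholds, repeated words and self-rated difficulty all depend to some degree on effort and expectation.

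Two things are at stake. An arm-related shift in the reference passes straight into the benefit score. And K-HINT, K-APHAB and free-field speech in quiet are left with no value of their own that was fixed before allocation and could be used to check balance or adjust later comparisons.

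**Working it through.** The point turns on the order of procedures, and the plan gives no figure for it. The check is therefore to ask, test by test, whether an unaided reference exists and whether anything before randomisation could serve as that reference.

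| Measure | Unaided half? | Possible pre-randomisation source | Placed after allocation as written? |
|---|---|---|---|
| Speech in quiet | Yes (Speech Audiometry) | None: screening WRS uses headphones, most comfortable level and another word list; this test is free field at 50 dB HL | Yes |
| K-HINT | Yes (Speech Audiometry) | None: no screening counterpart | Yes |
| K-APHAB | Yes (Questionnaires) | None: no screening counterpart | Yes |
| Functional gain | Yes (Functional gain) | Possibly the headphone PTA; the text does not say | Only if new thresholds are measured |
| REM | No: real-ear insertion gain is compared with the NAL-NL2 target after fitting (REM Assessment) | Not needed | Not affected |
| K-IOI-HA | No: it rates the aid only (Questionnaires) | Not needed | Not affected |

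**How a shift would travel.** Let *s* be the difference between arms in reporting or response bias in a visit 1 unaided value.

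- Visit 1 benefit = unaided − aided (or the reverse), so the arm difference at visit 1 moves by *s*.
- If the unaided value is remeasured at each visit and only visit 1 is shifted, the three-visit average of the arm difference moves by (*s* + 0 + 0)/3 = *s*/3, and the 1-year value does not move.
- If the visit 1 unaided value is carried forward, the benefit at every visit moves by *s*, including functional gain at 1 year, which the Objectives section names as the primary outcome.

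The average matters because the Statistical Analysis section plans a repeated-measures analysis with device type and time as factors.

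**Scale, for illustration only.** Number per arm: 64 × (1 − 0.15) = 54.4, or about 27 per arm, from the Sample Size section. The SD of functional gain is not in the document; 6 dB is assumed.

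- Standard error of the arm difference = 6 × √(2/27) = 1.63 dB.
- An assumed *s* of 2 dB is 2/1.63 = 1.2 standard errors; an assumed *s* of 3 dB is 3/1.63 = 1.8.

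These lines show only what a shift of that size would mean if it occurred and were carried forward. They are not evidence that it would occur.

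**Sample size.** The stated total of 56 reproduces with a one-sided two-sample t-test at *d* = 0.9, alpha .05 and power .95 (28 per arm, power 0.954). Reordering visit 1 changes none of these inputs.

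**The case against.** The strongest reply is that the article fixes the order of blocks, not of runs within a block. The speech and functional-gain sections speak of the state before and after wearing the aids without giving a time for the former, and a condensed article may leave such detail to the full protocol. This has some force. But the order that the article does state is explicit, and no section gives the unaided parts an earlier slot. Staff who follow the text would run them after fitting.

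Four further objections stand and limit the point:

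- **Source of the unaided thresholds.** The Functional gain section does not mention sound field. The screening PTA, also taken in a double-walled booth, could supply the unaided thresholds. The primary outcome is therefore affected only conditionally, even at visit 1.
- **Reach to 1 year.** Functional gain is measured at every visit. If the unaided thresholds are repeated at 1 year, the order at visit 1 has no bearing on the primary gain. Those later unaided values would be open-label whatever is done at visit 1.
- **Testers.** A reader might infer that the testers are unblinded. The article says this only of participants and care providers and is silent on testers. The participants' own knowledge is enough for the concern.
- **Nature of the reference.** A reader might infer that every benefit measure lacks a true baseline. K-IOI-HA and REM have no such unaided half. For the others, no period of device use has yet occurred, so the risk is response bias and not a treatment effect on the reference. Headphone PTA and WRS are collected before allocation and allow a partial balance check; PTA is also a natural covariate for a threshold-based outcome.

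**Conclusion.** The point holds in limited form. As the Participant Timeline section is written, the visit 1 unaided references for speech in quiet, K-HINT and K-APHAB are obtained once participants know their allocation. The same is true of functional gain if its unaided thresholds are not the screening PTA. The exposure is greatest for K-APHAB, which is self-reported, has no pre-randomisation counterpart and is a secondary measure.

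The documents do not support the stronger conclusion that the 1-year primary comparison is biased. That would need new unaided thresholds at visit 1, carried forward to 1 year, and a response shift that differs by arm. The first two conditions are not settled by the text, and the size and direction of the third cannot be derived from it. The 1.2 to 1.8 standard errors above rest wholly on an assumed SD of 6 dB and an assumed shift of 2 to 3 dB.

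This is an avoidable source of bias that costs very little to remove. It is not a flaw that invalidates the design.

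**What to change.** Rewrite the visit 1 sequence in the Participant Timeline section as follows:

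1. Screening tests.
2. The unaided parts of functional gain, speech in quiet, K-HINT and K-APHAB.
3. Randomisation.
4. Fitting.
5. The aided parts, with REM and K-IOI-HA as now planned.

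Name the pre-randomisation unaided values as the baseline. State in the Functional gain section whether the unaided thresholds are the screening PTA or a separate measurement, and whether later gains use the visit 1 value or a repeat. Split the unaided and aided rows in Table 1 to match. A line on whether the testers are masked would settle the remaining uncertainty.

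The cost is small: the same tests on the same day, with no change in sample size. The one downside is that anyone who leaves between the unaided tests and randomisation has been tested for nothing. The Results section reports that no patient had been enrolled when the article was written, so on that account the order could be changed before the first participant.

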**Screening tests**														
	PTA^b^		✓			—			—					
	WRS^c^		✓			—			—					
	Otoscopy		✓			—			—					
	Tympanometry		✓			—			—					
**HA^d^ provision and fitting**				✓			✓			—				
**Main tests**														
	**Functional gain**		✓			✓			✓					
	**Speech audiometry**													
		Quiet	✓			✓			✓					
		Noisy (K-HINT^e^)	✓			✓			✓					
	**REM^f^**		✓			✓			✓					
	**Questionnaires**													
		K-APHAB^g^	✓			✓			✓					
		K-IOI-HA^h^	✓			✓			✓					
**HA return**					—			—			✓			

^a^Not applicable.

^b^PTA: pure-tone audiometry.

^c^WRS: word recognition score.

^d^HA: hearing aid.

^e^K-HINT: Korean version of the Hearing In Noise Test.

^f^REM: real-ear measurement.

^g^K-APHAB: Korean version of the Abbreviated Profile of Hearing Aid Benefit.

^h^K-IOI-HA: Korean version of the International Outcome Inventory for Hearing Aids.

### Ethical Considerations

The study will be conducted in accordance with the principles outlined in the Declaration of Helsinki. Furthermore, it has received approval from the Institutional Review Board (IRB) of Samsung Medical Center (IRB 2023-04-149). Informed consent must be obtained prior to any clinical trial-related activities. Before participants join the clinical trial, the researcher will explain the trial process to them, obtain a signed consent form, and provide a copy of the consent form to the participants. Participation in the trial is voluntary, and consent can be withdrawn at any time.

To ensure privacy and confidentiality, no personally identifiable information will be recorded in any documents where trial results are documented, and participant identification will be coded. Screening numbers will be assigned sequentially as OTC_01, _02, etc, and documents linking the code to participant identities will be attached to the researcher’s file and stored in a locked cabinet. All clinical trial data collected and stored at the research institution may be kept for up to three years after the trial concludes.

If participants agree to take part in the study, they will not incur any costs for the tests conducted as part of the trial; however, they will be responsible for hospital admission fees, any tests unrelated to the trial, and consultation fees. The trial involves three visits in total, and participants will receive $50 for transportation costs at each visit. However, if a participant does not meet the inclusion criteria, drops out, or withdraws from the trial, transportation costs will not be provided.

## Results

This study is scheduled to begin in August 2024. The trial is currently in the recruitment phase after receiving IRB approval; however, no patients have been enrolled yet. The study will be conducted over 2 years, from August 2024 to July 2026. Each participant will have 2 follow-up visits at 6-month intervals, making the total follow-up period 1 year.

## Discussion

### Expected Findings

The purpose of this study is to conduct a noninferiority RCT comparing OTC HAs with traditional HAs to assess the clinical effectiveness of OTC HAs. The expected findings of the study are that OTC HAs will demonstrate noninferiority to traditional HAs in terms of functional gain. This means that OTC HAs will provide similar performance to traditional HAs. Recent research has focused on the clinical effectiveness of personal sound amplification products; however, there is still a lack of studies on the clinical effectiveness of OTC HAs, as they have only recently been introduced. To the best of our knowledge, this study is the first to investigate and potentially confirm the noninferiority of OTC HAs compared with traditional HAs. These findings could have significant implications for the accessibility and affordability of HAs, providing more options for individuals with HL.

### Strength and Limitations

The strengths of this study include its innovative approach, being the first to conduct a noninferiority RCT comparing OTC HAs with traditional HAs, thus addressing a significant gap in the existing literature. The clinical relevance is noteworthy, as assessing the clinical effectiveness of OTC HAs provides valuable insights that could influence clinical practice and policymaking. Furthermore, the findings from this study could have substantial implications for the accessibility and affordability of HAs, potentially offering more affordable options for individuals with HL. The study uses rigorous RCT methodology to ensure reliable and valid results, enhancing the credibility of the findings. Finally, the study’s timeliness is significant, as OTC HAs have only recently been introduced, and this research addresses a current need for evidence on their clinical effectiveness.

The limitations of this study include a short-term focus, as it may primarily address short-term outcomes, potentially overlooking longer-term effectiveness and user satisfaction with OTC HAs. In addition, the generalizability of results may be limited to specific populations and settings and may not extend to all individuals with HL or different health care systems. There is also a risk of potential bias, as with any RCT, where selection bias or other unforeseen biases could affect the results. Furthermore, technological variability in the OTC HAs available on the market could influence the outcomes, making it challenging to generalize findings across all OTC HAs. Finally, the study’s scope may be limited, as it may not address all potential factors influencing the effectiveness of HAs, such as user preferences, ease of use, or long-term adherence to using the devices.

### Conclusions

Since 2022, the introduction of OTC HAs has brought significant developments in the field. The availability of OTC HAs has resulted in a notable shift in how patients with HL can access and obtain these devices. With OTC HAs now being sold directly to consumers without the need for a prescription from HHPs, there is growing anticipation and curiosity surrounding their clinical effectiveness. Researchers, clinicians, and the general public are keen to explore the extent to which these devices can provide meaningful improvements in hearing ability and overall quality of life. As a result, there is a previous demand for studies to evaluate the clinical effectiveness of OTC HAs. With the wider availability and accessibility of OTC HAs, it is anticipated that more individuals will be inclined to try these devices as a potential solution for their HL. The increased usage will likely contribute to a wealth of real-world data and experiences that can be analyzed to further understand the benefits and limitations of OTC HAs. Researchers and HHPs will closely monitor the outcomes and feedback from users to gain insights into the effectiveness, user satisfaction, and overall impact of OTC HAs on hearing rehabilitation.

## Abbreviations

HA: hearing aid
HHP: hearing health care professional
HL: hearing loss
IRB: Institutional Review Board
K-APHAB: Korean version of the Abbreviated Profile of Hearing Aid Benefit
K-HINT: Korean version of the Hearing In Noise Test
K-IOI-HA: Korean version of the International Outcome Inventory for Hearing Aids
NAL-NL2: National Acoustics Laboratories–Non-Linear Prescription, second generation
OTC: over-the-counter
PTA: pure-tone audiometry
RCT: randomized controlled trial
REM: real-ear measurement
RTS: reception threshold for speech
WRS: word recognition score
